### Statistical analysis

Demographic and baseline characteristics of the participants will be described using frequencies and percentages for categorical variables and mean, standard deviation or median and interquartile range for continuous variables, as appropriate. Bivariate analyses will be performed estimating odds ratios for categorical variables and mean differences for continuous variables as well as their respective 95% CI. Multiple imputations by chained equations will be used to replace baseline missing values. Case-complete and imputed data results will be compared as a sensitivity analysis. The raw and adjusted HRs for adherences will be calculated for outcome events using Cox proportional hazard regression models, and proportionality of hazards assumption will be tested. Association analyses between adherence to study drugs, incidence of the endpoints or sick leave, and drug therapy (objectives 1, 2 and 3) will be analysed by means of generalized linear models. Objectives 4 and 5 are descriptive and they will be described using frequencies and percentages as appropriate.

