The main objective of our study is to assess the relationship between adherences to the four pharmacological groups recommended for secondary prevention and the clinical outcomes of cardiovascular morbidity and mortality in patients with established CHD. The outcomes which are included as components of the composite endpoint are all-cause mortality, ACS, and ischaemic stroke. The secondary objectives are: 1) to assess the incidence of the composite endpoint in patients who are adherent to treatment with all four drugs compared with patients who are adherent to any combination of three, two or one drug, or no drug; 2) to assess the relationship between baseline sociodemographic and clinical characteristics and adherence to drug therapy; 3) to compare the number of days on sickness leave due to any cause according to adherence to drug therapy; 4) to estimate prevalence of use of the four drug treatments; and 5) to describe the posology prescribed for the four drug treatments.

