### Data Collection and Data Sources

Diagnoses for study inclusion and endpoints will be obtained from CMBD-HA, which contains diagnoses at hospital discharge from all ICS hospitals, coded with International Classification of Diseases, Nineth Revision (ICD-9) [14]; see Table 1.

The rest of the variables will be captured from SIDIAP, which contains anonymized clinical information of all 279 PHC centres managed by the ICS in Catalonia (North-East Spain), covering a population of more than 5.8 million patients (about 80% of the total of 7.5 million population in Catalonia). The information contained in SIDIAP is registered by PHC general practitioners (GP), nurses and administrative staff in ECAP (electronic health records in ICS): comprehensive sociodemographic information, health conditions registered as ICD10 codes [15], specialist referrals, clinical parameters, toxic habits, PHC laboratory test results, GPs prescriptions and their corresponding pharmacy invoice data registered as Anatomical, therapeutic, chemical classification system (ATC) codes [16], date of sickness leave due to any cause, and date of death. Several reports have shown that SIDIAP data is useful for epidemiological research [17-25]. SIDIAP is listed under the European Network of Centres for Pharmacoepidemiology and Pharmacovigilance (ENCePP) resources database [26].

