#### Secondary Endpoints

The secondary endpoints will be AMI, unstable angina, ischaemic stroke, all-cause mortality, overall number of days on sickness leave due to any cause and due to CVD events, prevalence of use of the four pharmacological groups of interest, posology of the four pharmacological groups of interest.

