### Other Variables

All the following variables will be considered as potential confounders or effect modifiers in the association between adherence to the drug therapy and risk of the composite endpoint. They will be captured from SIDIAP database:

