#### Patient Baseline Characteristics

All sociodemographic characteristics will be measured on the index date: index year, number of visits to PHC, age, sex, MEDEA index (socioeconomic deprivation index) [27], smoking status, alcohol intake, height, weight, Body Mass Index (BMI); the information comes primarily from a codified variable. If the patient has no information, it is calculated from height and weight and physical activity.

**Table 3 table3:** ICD-10 codes for comorbidities of interest or diseases for exclusion

ICD-10 code	Description
I24*, I25*	Coronary heart disease
I63*, I65*, I66*, I67.2, I67.8	Ischaemic stroke
G45	Transient cerebral ischaemic attack
I70*, I73*, I74*	Peripheral vascular disease
E78*	Dyslipidaemia
I10*, I15*	Hypertension
E10*, E11*	Diabetes mellitus
I48	Atrial fibrillation
I50*	Heart failure
C00*-C97*	Malignancies
J40*-J44*	Chronic obstructive pulmonary disease
F30*-F39*	Depression
M05*, M06*, M15*-M19*	Arthritis (osteoarthritis or rheumatoid arthritis)
M80*, M81*	Osteoporosis
N18*	Chronic kidney disease
B20*-B24*	HIV
G30*, G31*	Alzheimer’s disease, other dementias

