#### Comorbidities and Clinical Parameters

They will be measured closest to the index date: type of cardiovascular event at index date (AMI and unstable angina and other forms of ACS captured from CMBD-HA), presence of coronary angioplasty implant after the event (data source CMBD-HA), cholesterol and other lipid parameters (low density lipoprotein-cholesterol, high density lipoprotein-cholesterol, total-cholesterol, and triglycerides), blood pressure measured (systolic and diastolic blood pressure), glycated hemoglobin, glomerular filtration rate, serum creatinine, specific comorbid conditions (see ICD-10 codes in Table 3), Charlson comorbidity index [28,29].

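### The published covariate list omits sick leave before the ACS, and the model comparing sick-leave days by adherence (secondary objective 3) names no covariates

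*Protocol article*

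**What the plan says.** Secondary objective 3, at the end of the Introduction, is "to compare the number of days on sickness leave due to any cause according to adherence to drug therapy". The Secondary Endpoints section lists "overall number of days on sickness leave due to any cause and due to CVD events".

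The Statistical analysis section groups this with two other objectives, "Association analyses between adherence to study drugs, incidence of the endpoints or sick leave, and drug therapy (objectives 1, 2 and 3"), and says that they "will be analysed by means of generalized linear models". It gives no family, link or covariates for these models. The word adjusted is attached there to the Cox hazard ratios, and the Discussion likewise describes adjustment only for Cox regression.

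The covariates are introduced under Other Variables as "potential confounders or effect modifiers in the association between adherence to the drug therapy and risk of the composite endpoint". The list that follows is detailed. Patient Baseline Characteristics opens with "index year, number of visits to PHC, age, sex, MEDEA index (socioeconomic deprivation index"), and Comorbidities and Clinical Parameters includes "specific comorbid conditions (see ICD-10 codes in Table 3), Charlson comorbidity index". Neither section, nor Concomitant Drug Use, nor Table 3 mentions sick leave before the index date or whether the patient was on leave at that date.

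The source of the outcome is dated. Data Collection and Data Sources says that SIDIAP holds "date of sickness leave due to any cause, and date of death". No look-back period is stated.

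**The concern.** Patients choose whether to keep refilling their prescriptions, so nothing balances prior sick leave between adherent and nonadherent groups. Leave for any cause includes leave for conditions that predate the ACS (depression and arthritis are both in Table 3). Unless a rule excludes it, it also includes leave already under way on the index date. Adherence after the ACS cannot have caused those days. The most direct measure of this tendency is the patient's own sick leave before the ACS, and it is the one variable of this kind that the list lacks.

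This goes beyond detail that a condensed article may leave to a fuller document. The article publishes a long and specific list and ties it to another endpoint. Even if the whole list were carried over to the sick-leave model, the pre-index value of the outcome would still be missing. Data extraction also tends to follow the listed variables, so a look-back that is not specified may not be obtained.

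At stake is a report of fewer sick days in adherent patients when some or all of the gap existed before the ACS. A lesser cost is variance that a baseline value could have removed.

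**Working it through.** **The plan's own figure.** The Sample Size section gives 3415 ACS cases in 2009-2011, an ICS share of about 30% and a 10-year study period. 3415 / 3 × 10 × 0.30 = 3415, against about 3400 stated, so the count reproduces. It is a feasibility count and does not test this point. The article gives no SD, correlation, power or expected difference for sick leave.

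**Assumed inputs.**
- Correlation between prior and later leave: ρ = 0.3 to 0.5 for bias, 0.2 to 0.6 for precision.
- Prior gap between adherence groups: d = 0, 0.1 or 0.2 SD.
- Share adherent to all four drugs: 25%. The only related figure in the article is 47.6% for three or more groups, from the Spanish cohort of 7462 ACS survivors. A range of 15% to 47.6% is shown below.
- Share of the cohort in work: 100% or 30%. Study Population admits all adults aged 18 or over, with no restriction to people in work.

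**Bias when adherence has no effect.** Using a normal approximation, in SD units:
- Spurious difference = ρ × d.
- SE = √(1/n₁ + 1/n₀).
- Two-sided 5% rejection = Φ(ρd/SE − 1.96) + Φ(−ρd/SE − 1.96).

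All 3400 contribute, 25% adherent: n₁ = 850, n₀ = 2550, SE = 0.0396. With 30% in work: 1020 patients, n₁ = 255, n₀ = 765, SE = 0.0723.

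| d | ρ | Spurious difference (SD) | Rejection, N = 3400 | Rejection, N = 1020 |
|---|---|---|---|---|
| 0 | any | 0 | 5% | 5% |
| 0.1 | 0.3 | 0.03 | 12% | 7% |
| 0.1 | 0.5 | 0.05 | 24% | 11% |
| 0.2 | 0.3 | 0.06 | 33% | 13% |
| 0.2 | 0.5 | 0.10 | 71% | 28% |

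Over the four rows with a gap, the range at N = 3400 is 10% to 55% if 15% are adherent and 14% to 83% if 47.6% are. At N = 1020 the corresponding ranges are 6% to 21% and 8% to 36%.

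**Precision.** Adjusting for the prior value multiplies the SE by √(1 − ρ²), and 3400 patients then act like 3400 / (1 − ρ²).

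| ρ | SE factor | Equivalent N |
|---|---|---|
| 0.2 | 0.98 | 3542 |
| 0.3 | 0.954 | 3736 |
| 0.5 | 0.866 | 4533 |
| 0.6 | 0.80 | 5312 |

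At correlations of 0.2 to 0.3 the SE falls by only 2% to 5%. These formulas are linear and Gaussian. The planned model is a generalized linear model of unstated family, for a count of days that probably has many zeros, so both tables show orders of size and are not forecasts.

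**The case against.** The strongest reply is that the article never says the sick-leave model is unadjusted. It names no covariates for that model, and a full protocol or analysis plan may do so. This stands. A reader might infer an unadjusted comparison because adjustment is mentioned only beside Cox models, but that is an argument from silence. The sentence that ties the list to the composite endpoint does not forbid using it elsewhere, and secondary objective 2 already uses baseline characteristics for another purpose. What the reply does not meet is that prior leave is absent from the list itself.

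Second, listed variables such as depression, arthritis, the Charlson index, primary-care visits, age and deprivation could absorb part of a prior difference if they are used. This also stands, and the table above gives them no credit. They remain indirect measures of prior leave. Days due to CVD events, also listed as an endpoint, are less exposed to leave for unrelated conditions.

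Third, usable prior data are inferred. The article gives no start year for the sick-leave field, and eligibility requires follow-up after the index date but no observation before it. History may be short for index dates in 2006. This limits the remedy but does not remove the reason for it.

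Fourth, bias needs a prior gap and a correlation with later leave, and the article gives neither. The larger rates also assume that all 3400 patients can contribute sick leave. Both points are accepted, and for that reason the ranges include no gap and 30% in work.

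**Conclusion.** The point holds as an omission from the published covariate list, with a conditional consequence. Under assumed prior gaps of 0.1 to 0.2 SD, correlations of 0.3 to 0.5 and 25% adherent, the spurious difference is 0.03 to 0.10 SD. The chance of a false-positive adherence effect runs from about 7-28% (30% in work) to about 12-71% (all contribute), against a nominal 5%. With no prior gap the bias is zero. Confounding is the main argument, because the precision gain is small at low correlations.

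The documents do not support the stronger reading that existing differences in sick leave will be reported as an adherence effect. They show no such difference and do not state that the model is unadjusted. Only a secondary objective is affected; the primary composite endpoint is not.

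**What to change.** In Patient Baseline Characteristics, add two variables derived from the SIDIAP sick-leave dates: days of sick leave for any cause in the 12 months before the index date, and on sick leave at the index date (yes/no). Where look-back is shorter than 12 months, express the first as a rate over the days observed.

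In Statistical analysis, name the covariates of the objective 3 model: these two variables plus the confounders in Patient Baseline Characteristics and in Comorbidities and Clinical Parameters, as measured at baseline. Show the result with and without days from leave that began before the index date.

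The cost is two derived variables from a source already used for the outcome, and a few lines of wording. The downside is incomplete look-back for some patients, notably in the early index years. Where there is no usable history, the multiple imputation already planned for missing baseline values could be used, and the number of such patients should be reported. Adjusting for prior days does not settle who in the cohort is able to take sick leave, which is a separate question.

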### Study Period

Inclusion period was between 2006-2015. The follow-up period was up to 2016.

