### Study Population

The study population includes individuals ≥18 years with an incident diagnosis of ACS during the study period 2006-2015, with at least two months of follow-up in the Information System for Research in Primary Care (SIDIAP) [12] after the index date. The next patients will be excluded: pregnant women on the index date; patients with a recorded diagnosis of ischaemic stroke in the six months prior to index date; patients living in a nursing home on the index date; and patients with Alzheimer’s disease or other dementias.

Case definition: patient with an incident diagnosis of ACS registered in CMBD-HA (dataset of diagnoses at hospital discharge) [13] of the Catalan Health Institute (ICS) within the period from 2006-2015. Index date definition: date of ACS episode.

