#### Primary Endpoint

The primary endpoint will be a composite endpoint of all-cause mortality, ACS and ischaemic stroke. From the index date (first episode of ACS), patients will be followed up to the end of follow-up or until a new diagnosis of any of the endpoints stated above. Patients who experience more than one endpoint during the study follow-up will be censored upon the first event of interest. Patients who do not experience any of the clinical events included in the composite endpoint during the follow-up will be censored at the last date of follow-up.

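### Secondary objective 1 analyses a censored endpoint by generalized linear models, with no person-time or fixed horizon stated, although potential follow-up runs from about 1 to 11 years

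*Protocol article*

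**What the plan says.** All places are in the protocol article.

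- **Objective.** The Introduction sets secondary objective 1 as "to assess the incidence of the composite endpoint in patients who are adherent to treatment with all four drugs", against patients adherent to three, two, one or none of them.
- **Endpoint.** Under Primary Endpoint, patients are followed from the index episode to the first component event. Those without one "will be censored at the last date of follow-up".
- **Follow-up.** Study Period reads: "Inclusion period was between 2006-2015. The follow-up period was up to 2016". Study Population asks only for patients "with at least two months of follow-up in the Information System for Research in Primary Care (SIDIAP") after the index date.
- **Models.** Statistical analysis first states: "The raw and adjusted HRs for adherences will be calculated for outcome events using Cox proportional hazard regression models". The next sentence takes adherence, incidence of the endpoints and sick leave together, "and drug therapy (objectives 1, 2 and 3) will be analysed by means of generalized linear models".

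No family, link, person-time offset or time horizon is attached to the generalized linear models (GLMs).

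**The concern.** The section does more than leave a detail open. Having named Cox regression for outcome events, it moves the graded comparison on the same composite to another model class. Objective 1 is the only listed objective that compares patients by number of drugs adhered to.

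The three objectives grouped in that sentence need different handling of time. Adherence (objective 2) is measured over a fixed eight months and needs no person-time. The composite (objective 1) is censored at very different times, and days of sick leave (objective 3) accumulate over unequal follow-up. An analyst could follow the sentence to the letter with a logistic model of event ever versus never.

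Two things would then be at stake. The OR or risk ratio (RR) would mix risks over periods from about 1 to 11 years and could not be compared with the HR of the main analysis. And if follow-up length differed between adherence groups, part of any association would reflect time at risk rather than adherence.

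**Working it through.** **Inputs from the article.** Inclusion 2006-2015 and follow-up to 2016 (Study Period); about 3400 cases (Sample Size); an HR of 0.72 for fully adherent versus nonadherent patients, cited in the Introduction and used here only as an illustration.

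**Assumptions.** Follow-up ends on 31 December 2016; uniform entry; constant hazard of 0.10 per year, with 0.05 to 0.15 as the range. The article gives no event rate.

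**The article's own figure.** 3415 cases / 3 years × 10 years × 0.30 = 3415, which agrees with the stated 3400 and is not in dispute.

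**Step 1: range of follow-up.** 1 January 2006 to 31 December 2016 is 11 years; 31 December 2015 to 31 December 2016 is 1 year. Observed follow-up may be as short as two months.

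**Step 2: dependence on follow-up length.** Risk by time t is 1 − exp(−h·t) in the reference group and 1 − exp(−0.72·h·t) in the adherent group. At h = 0.10:

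| t (years) | Reference risk | Adherent risk | RR | OR |
|---|---|---|---|---|
| 1 | 0.095 | 0.070 | 0.73 | 0.71 |
| 6 | 0.451 | 0.351 | 0.78 | 0.66 |
| 11 | 0.667 | 0.547 | 0.82 | 0.60 |

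The HR is 0.72 in every row. As t grows, the OR moves away from 1 and the RR moves towards 1. For h from 0.05 to 0.15, the 11-year OR runs from 0.66 to 0.54.

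**Step 3: false association with no true effect.** A patient entering s years after the start of 2006 has 11 − s years of potential follow-up and risk r(s) = 1 − exp(−h·(11 − s)), whatever the adherence. Let the adherent share p(s) rise linearly over the ten entry years. Average p·r, p·(1 − r), (1 − p)·r and (1 − p)·(1 − r) over s to obtain the four cells of the table, then take the crude OR and its Wald standard error at n = 3400 (two-sided 5% test, two adherence groups). At h = 0.10:

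| Assumed share, 2006 to 2015 | Crude OR | Significant in | OR stratified by index year (Mantel-Haenszel) |
|---|---|---|---|
| 40% to 50% | 0.93 | 20% | 0.999 |
| 30% to 50% | 0.85 | 62% | 0.998 |
| 30% to 60% | 0.79 | about 92% | 0.997 |

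For the middle row, h from 0.05 to 0.15 gives crude ORs of 0.87 to 0.83, significant in 40% to 73%. With no trend, the follow-up distributions are equal and the OR is 1.00.

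**Step 4: models that use time.** Take a rate of 8 per 100 person-years and mean potential follow-up of 5 years in adherent and 7 years in nonadherent patients (assumed, 200,000 simulated patients):

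| True ratio | Logistic OR | Poisson rate ratio, log person-time offset |
|---|---|---|
| 1.00 | 0.65 | 1.00 |
| 0.72 | 0.45 | 0.73 |

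Analytically, the Poisson model with offset returns the true ratio in every scenario examined.

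**The case against.** The strongest reply is that GLMs as a class do not ignore follow-up. A Poisson GLM with a log person-years offset handles unequal follow-up, suits the word incidence, and is one of the two remedies below. The sentence covers three different outcomes, so it may name only a model class, leaving family and offset to a fuller document. Cox HRs for adherence are planned in any case, and nothing restricts them to a binary exposure. Index year is among the listed potential confounders.

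Much of this stands. A reader might infer that the plan discards censoring, or that the comparison of 4, 3, 2, 1 and 0 drugs is bound to be distorted. The article supports neither. It does not say that follow-up time is ignored. A false association needs a model that ignores time, follow-up that differs by adherence, and no adjustment for that difference. The article shows no calendar trend in adherence, and step 3 shows that stratifying by index year brings the ORs to about 1.00. The rejection rates of 62% and about 92% therefore apply only to an unadjusted binary model.

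What does not stand is that this is only a detail left for later. The article does choose a model for objective 1, by number, and that choice departs from the censored-data model it has just named for the same kind of outcome.

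**Conclusion.** The point holds as a model assignment that should be completed or changed. It is not a demonstrated bias. A GLM is named for a censored composite, with potential follow-up of about 1 to 11 years and no statement of how time enters.

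If it is run as event ever versus never, the firm consequence is one of scale: HR 0.72 becomes an OR between 0.71 and 0.60 depending on follow-up, so the graded result cannot be read beside the main HR. This rests on the assumed hazard of 0.10 per year and an end of follow-up on 31 December 2016. A false association is conditional: the null crude OR of 0.85 depends on an assumed rise in adherence from 30% to 50% and essentially disappears on adjustment for index year. Early loss to follow-up that differs by adherence would not be dealt with by that adjustment.

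The issue concerns a secondary objective and leaves the main Cox analysis untouched.

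**What to change.** In Statistical analysis, take objective 1 out of the shared GLM sentence. State that it uses the same Cox model, time origin and covariates as the main analysis, with number of drugs adhered to (4, 3, 2, 1, 0) as a factor and a test for trend. If incidence rates are wanted, state instead a Poisson GLM with log person-years as offset. GLMs can stay for objectives 2 and 3, with observed time as offset for days of sick leave.

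The cost is one sentence and slightly more analysis. No new data are needed.
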